### Sample size calculation

This study is a small sample clinical trial, and as to be a preliminary for the further large sample clinical trial. Based on a previous study (46), PASS 15.0 software (NCSS Statistical Software, Kaysville, UT, USA) was used to determine the sample size, and by setting the MAS scores decreased in the three groups by 1, 0.75, and 0.45, respectively, with a standard deviation of 0.52, a two-sided *α* = 0.05 with 90% power, the minimum sample size was 24 cases per group. Considering a 20% dropout rate, 30 patients in each group and a total of 90 patients in three groups were needed.

### Data management

The data required for the study of all patients will be recorded on the printed case report forms (CRFs), including observation time points, outcome measures, adverse reactions, and safety evaluations. The private information of each participant, including name, phone number and other identity will be protected from disclosure. An independent data manager will check the accuracy and timeliness of the data and keep all data safe. No artificial data modification will be allowed after the end of the trial.

### Quality control

To ensure the high quality of the trial, all investigators and operators will be trained uniformly and professionally before the start of the trial. The training includes understanding the trial protocol and process and clarifying the tasks of each recruitment, treatment and evaluation step. During the implementation of the trial, the outcome data and safety will be reviewed and supervised by experts from the Ethics Committee of the Beijing University of Chinese Medicine.

### Statistical analysis

Statistical analyses will be performed by statisticians who are independent of the research team and have no knowledge of the study groupings or study settings. Statistical analyses will be performed using IBM SPSS Statistics 25.0 software and follow intention-to-treat (ITT) principles to ensure all subjects are included after randomization. Missing data will be handled by multiple imputations. Continuous variables that follow a normal distribution are presented as mean ± standard deviation, and those that do not follow a normal distribution are given as median and interquartile range. Comparisons within groups will be performed via paired t-tests, and difference among groups will be analyzed by the one-way ANOVA test. For measurements at different time points, differences were assessed using repeated-measures ANOVA followed by Bonferroni *post hoc* tests. The test level is 0.05, with *p* < 0.05 indicating a statistically significant difference.

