**Methods:**

A total of 90 post-ischemic stroke patients with spastic hemiplegia will be intervened for 4 weeks and followed up for 4 weeks. They will be randomly assigned to three groups including two observation groups and a standard care control group in a 1:1:1 ratio. All patients will receive standard care and regular rehabilitation accordingly. In addition, the two observation groups will receive 12 sessions of Acu-TENS at 20 Hz or 100 Hz for 30 min combined with 1 mA tDCS for 20 min, three times a week, for 4 weeks. The primary outcome is the change in total modified Ashworth scale (MAS) score from baseline to week 4. Secondary outcomes include changes in surface electromyography (SEMG), Fugl-Meyer Motor Function Scale, Modified Barthel Index (MBI), and 10-meter walk test from baseline to week 4. MAS score will also be measured after 4 weeks of follow-up. Adverse events throughout the study will be recorded.

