### Participants

#### Inclusion criteria

Patients meet all of the following criteria will be considered as eligible participants.

Patients with ischemic stroke confirmed by CT or MRI, with first onset of stroke, and onset of stroke for more than 1 month.The clinical symptoms include unilateral limb paralysis and motor dysfunction of upper and lower limbs.The modified Ashworth scale (MAS) rating of grade I or above for the major involved joint of the limb.Able to walk independently for 10 meters without help.Aged ≥18- years, regardless of gender.Stable state, clear consciousness, and no hearing and comprehension disabilities to complete the questionnaires.Participate voluntarily and sign an informed consent form.

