### Outcome measurement

#### Primary outcome

The primary outcome will be the change from baseline in muscle tone assessed with MAS in elbow, wrist, knee, and ankle 4 weeks after baseline (the end of the intervention). The detailed scoring rules of MAS with 6-level (level 0, 1, 1+, 2, 3, 4) are consistent with previous study (41). In the analysis of MAS scores, a derived MAS score with a 6-point scale from 0 to 5 (level 0, 1 equivalent to 0 and 1 respectively, level 1+ transformed into 2, 2 into 3, 3 into 4, and 4 into 5) will be used for practicality. To ensure the objectivity and accuracy of the MAS assessment, the independent evaluator will be instructed via specific training to use a medium velocity of passive movements, lasting about 1 s (42). Subsequently, MAS will be measured for above mentioned four joints with different levels in each joint, and then the sum of MAS scores in four joints will be recorded as the total MAS score.

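### The planned group comparison of change in total MAS makes no use of baseline MAS; ANCOVA on baseline would usually be more precise, by an amount the documents do not determine

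*Protocol article*

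**What the plan says.** The abstract defines the endpoint: "The primary outcome is the change in total modified Ashworth scale (MAS) score from baseline to week 4". The Primary outcome section agrees and adds that "the sum of MAS scores in four joints will be recorded as the total MAS score". Each joint is rescored 0 to 5, so the total runs from 0 to 20. Table 1 schedules MAS at week 0 for all participants, then at weeks 1 to 4 and week 8. Every secondary outcome is measured at baseline and week 4.

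For entry, the Inclusion criteria require "The modified Ashworth scale (MAS) rating of grade I or above for the major involved joint of the limb". The Randomization and blinding section describes 1:1:1 allocation and no stratification by severity.

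For comparisons between groups, the Statistical analysis section states that "difference among groups will be analyzed by the one-way ANOVA test". For measurements at several time points it says that "differences were assessed using repeated-measures ANOVA followed by Bonferroni" post hoc tests. It does not say which of the two applies to the primary outcome. Neither is given a baseline covariate.

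**The concern.** A change score subtracts the whole baseline value, which is the best use of baseline only if the regression slope of week 4 on baseline is 1. When the slope is below 1, two things follow. The change score carries avoidable variance, so the standard error is larger than it need be. Also, an arm that by chance starts with higher MAS tends to show a larger fall whatever its treatment, and the unadjusted contrast includes that difference.

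With 30 per arm, some imbalance in baseline MAS is to be expected. What is at stake is the precision of the group differences, above all the 20 Hz versus 100 Hz contrast on which the choice of frequency depends, and how far the estimates can be trusted if the arms differ at baseline. The validity of the test is not at stake.

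**Working it through.** **Inputs from the protocol (Sample size calculation):** mean falls in MAS of 1, 0.75 and 0.45; SD 0.52, taken here as the SD of the change in total MAS; two-sided alpha 0.05; 90% power; 24 per group, 30 after 20% dropout.

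**Assumptions not in the protocol:** the baseline to week-4 correlation r, shown as a range, and equal variances at the two times.

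**1. The plan's own figure.** The mean of the three falls is 0.7333, and the squared deviations sum to 0.1517. The noncentrality at 24 per group is 24 × 0.1517 / 0.52² = 13.46. The noncentral F with 2 and 69 degrees of freedom gives power 90.5%; at 23 per group it is 89.2%. The minimum is therefore 24, and 24 / 0.8 = 30. The stated size is that of an unadjusted one-way ANOVA on change.

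**2. Variance with and without baseline.** With common SD s:
- Var(change) = 2s²(1 − r)
- ANCOVA residual variance = s²(1 − r²)
- ratio = (1 + r)/2

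**3. Effect at 24 per arm.** The change SD is held at 0.52. The unadjusted pairwise SE is 0.52 × √(2/24) = 0.150. For ANCOVA, the variance is multiplied by (1 + r)/2 and by 1 + 1/67 for estimating the slope, and the error degrees of freedom fall from 69 to 68.

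| r | variance ratio | pairwise SE | change in SE | omnibus power |
|---|---|---|---|---|
| unadjusted | 1 | 0.150 | – | 90.5% |
| 0.3 | 0.65 | 0.122 | −19% | 98.3% |
| 0.5 | 0.75 | 0.131 | −13% | 96.6% |
| 0.7 | 0.85 | 0.139 | −7% | 94.3% |
| 0.9 | 0.95 | 0.147 | −2% | 91.6% |
| 0.95 | 0.975 | 0.149 | −0.5% | 90.8% |
| 0.98 | 0.99 | 0.150 | +0.2% | 90.4% |

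Simulation with 20,000 trials per value of r gave ANCOVA power of 98.4%, 96.5%, 94.2%, 91.4% and 90.0% at r = 0.3, 0.5, 0.7, 0.9 and 0.98, against 90–91% for the unadjusted test.

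**4. Which r fits the plan's SD.** Rearranging step 2, r = 1 − 0.52²/(2s²).
- r = 0.3, 0.5 and 0.7 need a baseline SD of 0.44, 0.52 and 0.67, which is narrow on a 0–20 scale.
- A baseline SD of 1 gives r = 0.865 and power 92.1%.
- A baseline SD of 2 gives r = 0.966 and power 90.6%.
- A baseline SD of 3 gives r = 0.985 and power 90.3%.

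A wide baseline and a change SD of 0.52 together therefore leave almost nothing to gain.

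**5. Conditional bias.** Suppose two arms differ at baseline by one standard error, s√(2/24). The unadjusted change contrast then shifts by (1 − r) times that amount: 0.089, 0.075, 0.058 and 0.034 at r = 0.3, 0.5, 0.7 and 0.9. Against the smallest planned adjacent difference (1 − 0.75 = 0.25), this is 36%, 30%, 23% and 13%.

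**6. Pairwise contrasts.** For differences of 0.25 and 0.30 at 24 per arm, with alpha 0.05 and no multiplicity correction, power is 38% and 52% unadjusted. With ANCOVA at r = 0.5 it is 49% and 64%.

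**The case against.** The strongest reply is that nothing is broken. In a randomised trial, ANOVA on change is unbiased over randomisation and keeps its type I error. The sample size reproduces for exactly this test, and the trial calls itself a pilot. All of that stands.

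A second reply is that the gain cannot be taken for granted, and this also stands. A reader might infer from the loose entry criterion that baseline totals spread over most of the scale, and that ANCOVA would therefore give a large gain. The two ideas conflict: with a change SD of 0.52, a wide baseline forces r towards 1 and the gain vanishes (step 4). The independent 10-metre walk required at entry also makes the top of the scale unlikely. If 0.52 is not a credible SD for the four-joint total, that is a separate sample-size question, and the absolute power figures here would change with it.

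A third reply is that the one-way ANOVA is not tied by name to the primary outcome, and that MAS at six time points may be meant for the repeated-measures ANOVA. The point survives either reading. With two time points, the group-by-time test is the ANOVA on change. With more, the model as described still has no baseline covariate.

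It may also be said that covariates are commonly left to a fuller document. Here, though, the article names the test, and that test has no baseline term.

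**Conclusion.** The point holds as a recommended improvement to efficiency and robustness; it is not a flaw in validity. Under equal variances and a change SD of 0.52, ANCOVA lowers the pairwise SE by 19% at r = 0.3, falling to 2% at r = 0.9. Omnibus power moves from 90.5% to about 98% at r = 0.3 and 92% at r = 0.9. Near r = 0.95–0.98 the two methods are practically equal, and the most ANCOVA loses there is a fraction of one per cent in SE. Since r is not documented, no single gain should be quoted.

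Three stronger conclusions are tempting but not supported:
- That ANCOVA is more precise whenever r is below 1. The slope has to be estimated, and that cost cancels the gain close to 1.
- That it removes chance imbalance. It adjusts only for measured baseline MAS, and a linear covariate does not cure a floor effect.
- That time since stroke onset must also enter the model. Nothing in the protocol quantifies its value as a covariate.

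**What to change.** In the Statistical analysis section, replace the one-way ANOVA for the primary outcome with ANCOVA: week-4 total MAS, or its change from baseline, on group with baseline total MAS as covariate. The two forms give the same adjusted group differences. Use the same form for each secondary outcome, with its own baseline value as covariate. Report adjusted mean differences with 95% confidence intervals. Do not add time since onset. Baseline values are already scheduled for every outcome, so the change is a sentence or two of text and one residual degree of freedom (68 instead of 69 at 24 per arm). The planned 30 per group need not change, and it should not be reduced on the strength of an assumed r.

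### The plan does not say which between-group test decides week-4 MAS, and the test it was sized on has no stated step for comparing 20 Hz with 100 Hz

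*Protocol article*

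**What the plan says.** The abstract defines one primary quantity: "The primary outcome is the change in total modified Ashworth scale (MAS) score from baseline to week 4". The Primary outcome section agrees on the time point, "4 weeks after baseline (the end of the intervention", and defines the total as the sum over elbow, wrist, knee and ankle.

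The abstract adds that "MAS score will also be measured after 4 weeks of follow-up". Table 1 puts MAS at weeks 0, 1, 2, 3, 4 and 8. Every secondary efficacy outcome is measured only at week 0 and week 4.

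The Statistical analysis section gives three rules and ties none of them to the primary outcome:
- Within groups: "Comparisons within groups will be performed via paired t-tests".
- Between groups: "difference among groups will be analyzed by the one-way ANOVA test".
- Over time: "For measurements at different time points, differences were assessed using repeated-measures ANOVA followed by Bonferroni" post hoc tests.

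One threshold covers all of them: "The test level is 0.05". The Sample size calculation uses a two-sided alpha of "0.05 with 90% power". It assumes MAS reductions of 1, 0.75 and 0.45 with a standard deviation of 0.52, and does not name the test.

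**The concern.** A change score at one visit fits the one-way ANOVA rule. MAS is also the only efficacy outcome with more than two visits, so the repeated-measures rule applies to it more than to anything else. The two rules test different hypotheses.

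- The one-way ANOVA of week-4 change asks whether the three arms differ at week 4. A significant result does not say which arms differ. No pairwise step follows it in the text, although finding the better frequency is a stated objective.
- The repeated-measures omnibus effects use every visit entered. The group effect averages in baseline, where randomised arms should not differ, and week 8. The group-by-time interaction spreads over (3−1)×(6−1) = 10 degrees of freedom. Neither is aimed at week 4.
- The only stated adjustment, Bonferroni, belongs to the repeated-measures analysis, and the plan does not say which contrasts it covers.

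At stake is whether two analysts following this section would reach the same primary conclusion, and whether the 20 Hz versus 100 Hz comparison at week 4 has any defined test.

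**Working it through.** **Inputs from the protocol.** Reductions 1, 0.75, 0.45; SD 0.52; alpha 0.05 two-sided; 24 per group; six MAS visits.

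**Inputs assumed.** Equal correlation between visits of 0.5 to 0.7. SD of the week-4 change 0.52. Effect growing linearly to week 4 and half retained at week 8, that is, visit weights 0, 0.25, 0.5, 0.75, 1, 0.5.

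**1. Reproducing the plan's sample size.** The mean reduction is 0.7333. The squared deviations sum to 0.0711 + 0.0003 + 0.0803 = 0.1517. The noncentrality is λ = n × 0.1517 / 0.52². At n = 24, λ = 3.64 / 0.2704 = 13.46 on 2 and 69 df, giving power 0.905. At n = 23 power is 0.892. So 24 is the smallest n reaching 90% for a one-way ANOVA F test, and 24/(1−0.2) = 30.

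**2. Repeated-measures group effect, same trial.** The visit weights average 3/6 = 0.5, so the differences in patient means are halved. The variance of a patient's mean over six visits is s²[(1−ρ)/6 + ρ], with s² = 0.52²/[2(1−ρ)].
- ρ = 0.5: s² = 0.2704, variance 0.1577, λ = 24 × 0.1517 × 0.25 / 0.1577 = 5.77, power about 0.54.
- ρ = 0.7: s² = 0.4507, variance 0.338, λ = 24 × 0.1517 × 0.25 / 0.338 = 2.69, power about 0.27.

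**3. Repeated-measures interaction.** The squared deviations of the visit weights from 0.5 sum to 0.25 + 0.0625 + 0 + 0.0625 + 0.25 + 0 = 0.625. The error variance is s²(1−ρ) = 0.1352 for any ρ. So λ = 24 × 0.1517 × 0.625 / 0.1352 = 16.8 on 10 and 345 df, and power is about 0.81.

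**4. Agreement, by simulation.** Under the planned means, one-way ANOVA and the interaction give different answers in about 15% of trials.

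**5. Error rates under no difference, by simulation.** Each test alone is near 5%. If success were claimed on any of the three, the rate would be about 13%. Three pairwise week-4 t-tests with no gate and no adjustment would give about 12%. The plan states neither use.

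**6. The pairwise step the objective needs.** Power at 24 per group for each gap between the planned means:

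| Gap | F test first, then unadjusted t | Bonferroni (0.05/3) |
|---|---|---|
| 0.25 | 0.37 | 0.22 |
| 0.30 | 0.50 | 0.32 |
| 0.55 | 0.90 | 0.88 |

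The gated procedure has a simulated familywise error of about 0.05. It is a closed test for three groups: if any two of the three pairwise equalities hold, all three means are equal, so the F test covers the only intersection hypothesis.

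**7. Paired t-test in the arm assumed to change by 0.45.** t = 0.45 / (0.52/√24) = 4.2, power about 98%. If that arm is standard care (the protocol does not label the three values), its within-group test will almost always be significant.

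**The case against.** The text supports a coherent reading. The primary outcome is one number per patient, which fits one-way ANOVA; the sample size reproduces as that test; and the repeated-measures rule can be read as covering the course of MAS over weeks 0 to 8. This is a condensed article of a self-described pilot, and the choice of effects and contrasts is often left to an analysis plan that is not shown. Most of this stands. It makes one-way ANOVA the likely intention and lowers the severity. It does not remove the point, because the section states two overlapping rules for the primary variable, and the likely primary test is given no step that serves the stated objective.

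A reader might infer three stronger things that the document does not support:
- **That Bonferroni protects only something other than week 4.** The contrasts are unspecified and could include between-group contrasts at week 4. Only the omnibus repeated-measures effects clearly do not target that visit.
- **That the plan carries a 12% or 13% false-positive rate.** Those rates need ungated, unadjusted pairwise tests, or a claim of success on any of three tests. Neither is written.
- **That paired t-tests are offered as evidence of efficacy.** They are assigned to within-group comparison only. The 98% figure shows why they should not be read as more than that.

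**Conclusion.** The point holds as a should-fix ambiguity. Week-4 MAS change can be analysed under two between-group rules with no deciding rule, and the one that matches the sample size lacks a pairwise follow-up. The primary conclusion can, but need not, depend on the choice.

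The reproduction of 24 per group rests on the protocol's figures alone. The power of the repeated-measures effects and the 15% disagreement rest on the assumed correlation and time course and would move with them. That the tests address different hypotheses does not depend on those assumptions.

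**What to change.** State in the Statistical analysis section:
- The primary analysis is the between-group comparison of week-4 change in total MAS, by ANCOVA with baseline total MAS as covariate.
- The 2-df group effect is tested at 0.05. Only if it is significant are the three pairwise contrasts tested, each at 0.05. All three differences are reported with 95% confidence intervals.
- The repeated-measures ANOVA and week 8 are supportive.
- Within-group paired t-tests are descriptive and are not evidence of efficacy.

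The cost is wording only: sample size and visits stay as they are, and the planned software can run the analysis. The one loss is that within-group p-values no longer have an inferential role. The gate does not make the trial well powered for the smaller gaps (0.37 for a gap of 0.25), so the 20 Hz versus 100 Hz result should be read mainly from its confidence interval.

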## Discussion

The majority of stroke survivors have sequelae including spasticity and motor disorder (47), which might severely weaken the self-care ability of patients, burden the families and public healthcare system. Relieving limb spasticity effectively is crucial to promote motor recovery in spastic hemiplegia after ischemic stroke (48). Increasing evidence showed that acupuncture and noninvasive acupuncture related therapies such as Acu-TENS are widely used for post-stroke spasticity with satisfied results (34, 35, 49). Meanwhile, tDCS also showed positive effects for post-stoke spasticity (28–30). However, to the best of our knowledge, in addition to investigating the effectiveness and safety of Acu-TENS on spasticity and motor function after stroke, few studies have screened the optimal frequency of TENS. Moreover, studies that include both TENS and tDCS based on classical acupuncture points are even more rare. This clinical trial is designed to focus on the optimal stimulation frequency of Acu-TENS in the treatment of post-stroke spastic hemiplegia, to preliminarily evaluate the efficacy and safety of Acu-TENS combined with tDCS therapy, and to offer physicians and patients an additional treatment option. The results will provide a reference for the setting of rated parameter of related mixed transcutaneous and transcranial stimulation system for stroke rehabilitation.

### Elucidation of optimal stimulation parameters for Acu-TENS is essential for its effectiveness

Notably, spasticity rarely tends to resolve on its own but progressively worsens over time (50). Spasticity can exacerbate muscle weakness, leading to severe dyskinesia and further exacerbation of daily activities (51). Therefore, adequate and effective control of post-stroke spasticity is the key to break this vicious cycle, thereby fully facilitating motor recovery (48). Compared to medications and surgery, Acu-TENS therapy is a non-pharmaceutical and non-invasive modality that is more acceptable to patients.

The frequency used in an electrical stimulation therapy always plays a crucial role for its therapeutic effect. The frequency of Acu-TENS is worthy of exploring and researching, since it is used in variety, ranging from 2 to 100 Hz. Two Meta-analysis studies have shown that the frequency of TENS for post-ischemic stroke with spastic hemiplegia is mostly at 100 Hz (32, 33). TENS at 20 Hz has also been used in some studies, with positive effects of improving electromyography, relieving spasticity, and increasing walking speed (37, 52, 53). A very few studies compared the anti-spastic effects of TENS or TEAS at different frequencies in stoke patients. Only one study (36) investigated the effects of both 2 and 100 Hz of TEAS on muscle spasticity following brain injury, the results suggested that both low and high frequencies had anti-spastic effects while 100 Hz was better. Taken together, in this study, we will compare the effects of Acu-TENS at 20 and 100 Hz in treating post-ischemic stroke with spastic hemiplegia to explore the optimal Acu-TENS stimulation frequency. The results of this study could provide a reference for setting optimal rated parameters of noninvasive acupoint-based transcutaneous stimulator, which can be manipulated by patients themselves. This modulation may be an alternative option for some chronic diseases such as post-stroke sequelae, thereby promoting proactive rehabilitation of the elderly.

